## 5. TREATMENT OF SUBJECTS

### 5.1 Investigational product/treatment

Laparoscopic hernia repair will be performed according the PIRS technique by Patkowski et al (8). This approach will be done under general anaesthesia with muscle relaxation. The patient will be placed in supine position. The operation is as follows: Pneumoperitoneum is established by introducing a 3-5-mm reusable trocar through a sub-umbilical incision. Insufflation pressure is between 8–10 mm Hg. A 30-degree telescope is used and the whole peritoneal cavity is inspected. Any hernia is reduced manually or with the aid of the telescope tip. The location for the needle puncture is assessed by pressing the inguinal ring region from the outside with the tip of a Kocher or any other blunt surgical instrument. Under laparoscopic-guided vision the 16 or 18 gauge injection needle with nonabsorbable thread inside the barrel of the needle is introduced into the body, through the abdominal wall into the abdominal cavity. Needle movement is performed on the outside of the body under laparoscopic vision. With the movements of the tip of the needle the thread passes under the peritoneum, over half of the internal ring including a part of the ligament and adjacent tissue. The thread is pushed through the barrel of the needle into the abdominal cavity and eventually makes a loop. The needle is pulled out, leaving the loop of the thread inside the abdomen. From outside the patient's body, one of the thread ends is introduced again into the barrel of the needle and the needle passes through the same skin puncture point, to surround the other half of the internal ring with part of the round ligament. To prevent the vas deferens and testicular vessels from injury a small space is left above these structures. The end of the thread goes through the barrel of the needle into the thread loop and the needle is withdrawn. Next, the thread loop is pulled out of the abdomen with the thread end caught by the loop. In this way the thread is placed around the inguinal ring under the peritoneum and both ends exit the skin through the same puncture point. The knot is tied to close the internal ring and is placed under the skin. If a contralateral hernia or CPPV is found, it is closed during the procedure according to the same method as described above, regardless of its diameter. The umbilical wound is closed with absorbable stitches and covered with pressure dressing to prevent hematoma formation. The skin puncture point in the inguinal region is left without any dressing.

## **5.2 Use of co-intervention (if applicable)**

Open hernia correction is as follows: an incision is made in a skin line in the groin. The incision is carried down through the dermis to expose subcutaneous fat and Scarpa fascia. The Scarpa fascia is cut to expose the external oblique muscle. According to the surgeons' preference and/or opinion the external oblique is incised. The hernia sac is searched and if a hernia or PPV is absent, the procedure is finished by closure of Scarpa fascia and skin. If a hernia or PPV is found, the hernia is grasped and cord structures are elevated, creating an opening underneath the sac. An instrument is placed through the opening. Vas deferens and vessels (in boys) are dissected away from the hernia sac or PPV. The sac is then checked for contents. The sac is divided. The proximal sac is then cleaned to the level of the internal inguinal ring, twisted on itself and ligated at the level of the internal ring. The testis (in boys) is returned to the normal scrotal position. Scarpa fascia is closed with a suture. Skin is closed. During the open repair, no contralateral exploration will be performed in the case of a unilateral inguinal hernia.

## **5.3 Escape medication (if applicable)**

Not applicable.

**6. INVESTIGATIONAL PRODUCT**

Not applicable.

**7. NON-INVESTIGATIONAL PRODUCT**

Not applicable.

## 8. METHODS

### 8.1 Study parameters/endpoints

#### 8.1.1 Main study parameter/endpoint

Number of infants with an ipsilateral recurrent hernia or MCIH after operative repair requiring a reoperation within one year after primary surgery.

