| MCIH    | Metachronous contralateral inguinal hernia                                                                                                                                                                                                                                                                                                |
| METC    | Medical research ethics committee (MREC); in Dutch: medisch-ethische toetsingscommissie (METC)                                                                                                                                                                                                                                            |
| PIRS    | Percutaneous Internal Ring Suturing                                                                                                                                                                                                                                                                                                       |
| (S)AE   | (Serious) Adverse Event                                                                                                                                                                                                                                                                                                                   |
| SPC     | Summary of Product Characteristics; in Dutch: officiële productinformatie IB1-tekst                                                                                                                                                                                                                                                       |
| Sponsor | The sponsor is the party that commissions the organisation or performance of the research, for example a pharmaceutical company, academic hospital, scientific organisation or investigator. A party that provides funding for a study but does not commission it is not regarded as the sponsor, but referred to as a subsidising party. |

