**Main study parameters/endpoints:** Primary endpoint: Number of operations related to inguinal hernia within one year after inguinal hernia repair. Other endpoints: Duration of surgery, operative and postoperative complications, duration of hospital admission, postoperative pain, time to full recovery, CPPV-rate, cosmetic appearance and cost-effectiveness (health care and social costs). **Nature and extent of the burden and risks associated with participation, benefit and group relatedness:** Both the open and PIRS technique are commonly used techniques in paediatric inguinal hernia repair and are dependent of the surgeon performing the procedure. Therefore, no extra burden of risk exist regarding this study.

Both treatment strategies are currently performed in children with unilateral sainguinal hernia who need to undergo hernia repair. Consequently, there are no additional risks for subjects of this study and it is therefore not necessary to install a DSMB.

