## **2. OBJECTIVES**

This randomized controlled trial studies the difference between open and laparoscopic PIRS repair with total of operations related to inguinal hernia within one year after inguinal hernia repair as primary outcome measure. Other endpoints are duration of surgery, operative and postoperative complications, use of different anaesthetic techniques, duration of hospital admission, postoperative pain, time to full recovery, CPPV-rate, cosmetic appearance and cost-effectiveness (health care and social costs).

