### **4.4 Sample size calculation**

Reoperation includes both MCIH and recurrence rates. Since recent studies showed that the recurrence rate is similar between the open and laparoscopic group (0.3 vs 0.2% (12)), we used reoperation rates due to MCIH to calculate our sample size. The latest IPEG guidelines states that the MCIH rate after open repair is 6-8%. We expect that the laparoscopic repair reduces the MCIH rate to 1% since the CPPV will be closed during the same procedure. Thus, re-operation based on MCIH is performed in approximately 6% patients in the open group and in approximately 1% in the laparoscopic PIRS group. We consider a reduction of 5% of children requiring reoperation clinically relevant.

A total sample size of 422 patients is needed to detect such a reduction with a power of 0.80 at a two-sided alpha of 0.05 (nQuery Advisor 7.0). Taking into account 10% loss to follow-up we need to include 464 children. Since approximately 800-850 paediatric patients a year undergo inguinal hernia repair in our participating centres, we expect to reach our sample size within one to two years after the start of the trial. After one year of follow-up, we will perform an interim analysis to assess the effect of both treatment strategies.

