## 10. STATISTICAL ANALYSIS

### 10.1 Primary study parameter(s)

We will create a 2x2 contingency table with the children that underwent open or laparoscopic repair or not versus the children with and without a ipsilateral recurrent or MCIH hernia in the year after surgery. A chi-square test will be performed and the relative risk, absolute risk difference and odds ratio with their 95% confidence intervals will be calculated. In addition, effect modification will be assessed for gestational age, age at the time of surgery, sex and initial hernia side to identify whether the effect of a treatment is different in groups of patients with different characteristics. Mean differences and corresponding 95% confidence intervals will be calculated for duration of operations (including anaesthesia). Risk differences and 95% confidence intervals will be calculated for complications. Logistic regression analysis will be performed to adjust for possible confounders (i.e. prematurity, side of inguinal hernia), if necessary. All analyses will be performed according to the intention-to-treat principle. Missing values will be analysed using multiple imputation.

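### The primary endpoint is defined inconsistently, and its narrower wording leaves a recurrence on a contralateral side closed at the PIRS operation unclassified, in the PIRS arm only

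*Protocol*

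**What the plan says.** The protocol describes the primary endpoint in five places.

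- **Summary:** "Number of operations related to inguinal hernia within one year after inguinal hernia repair".
- **Section 2, Objectives:** "total of operations related to inguinal hernia within one year after inguinal hernia repair as primary outcome measure".
- **Section 4.4, Sample size calculation:** "Reoperation includes both MCIH and recurrence rates". No side is named for recurrence.
- **Section 8.1.1, Main study parameter:** "Number of infants with an ipsilateral recurrent hernia or MCIH after operative repair requiring a reoperation within one year after primary surgery".
- **Section 10.1, Analysis:** the 2x2 table sets treatment against "the children with and without a ipsilateral recurrent or MCIH hernia in the year after surgery".

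The abbreviation list expands MCIH as "Metachronous contralateral inguinal hernia" and adds no working definition. The definitions in section 8.1.2 cover testicular atrophy, wound infection and apnoea, but neither recurrence nor MCIH.

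The arms differ in what happens to the other groin. In the PIRS arm (section 5.1), "If a contralateral hernia or CPPV is found, it is closed during the procedure according to the same method as described above", whatever its diameter. In the open arm (section 5.2) the contralateral side is not explored when the hernia is unilateral.

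**The concern.** The first three descriptions would count a reoperation on either side. The last two limit recurrence to the ipsilateral side and leave the contralateral side to MCIH. For most events this makes no difference. It does for a child enrolled with a unilateral hernia in whom a contralateral hernia is found and closed at the PIRS operation, then recurs and is reoperated. That event is a hernia-related operation (summary, objectives) and a recurrence (section 4.4). But it is not an ipsilateral recurrence, and it is hard to call metachronous when the contralateral hernia was already present at the index operation. Under 8.1.1 and 10.1, read literally, it has no category.

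The open arm does not open the contralateral groin, so by protocol this event cannot occur there. Leaving it out can therefore only lower the PIRS count. The trial's hypothesis is that dealing with the contralateral side during the first operation prevents a second one, so the status of a failed contralateral closure should be explicit. Section 8.2 says that participants and investigators know the allocation, and the protocol describes no masked classification of the primary endpoint.

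**Working it through.** **Which later events count under 8.1.1 and 10.1**

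| Later event, reoperated within one year | Summary and objectives | Section 4.4 | Sections 8.1.1 and 10.1 |
|---|---|---|---|
| Ipsilateral recurrence, either arm | counts | counts | counts |
| Contralateral hernia, side untouched at index | counts | counts (MCIH) | counts (MCIH) |
| Contralateral hernia after closure of a CPPV only (PIRS) | counts | counts | most naturally MCIH, so counts; not stated |
| Recurrence of a contralateral hernia closed at index (PIRS) | counts | counts (recurrence) | not ipsilateral, not clearly metachronous |

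The last row is the gap. The third row is an ambiguity that one sentence would settle. The descriptions also differ in unit (operations or children), and 10.1 does not repeat the reoperation requirement of 8.1.1. A single definition would remove these differences too.

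**The plan's own figure.** Inputs from section 4.4: 6% open, 1% PIRS, power 0.80, two-sided alpha 0.05. Section 8.2 gives 1:1 allocation. With pooled variance and no continuity correction,

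n per arm = [1.960 × √(2 × 0.035 × 0.965) + 0.842 × √(0.06 × 0.94 + 0.01 × 0.99)]² / 0.05² = 210.9, rounded up to 211, or 422 in total.

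This reproduces the stated 422, so no stated number is in dispute. Expected events are 211 × 0.06 = 12.7 open and 211 × 0.01 = 2.1 PIRS.

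**Size of the gap.** Affected PIRS children = 211 × (share with the contralateral side closed) × (recurrence risk of a closed side).

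- Share closed: the protocol gives no figure. Assumed 20-60%.
- Recurrence risk: section 4.4 quotes 0.3% (open) and 0.2% (laparoscopic), the nearest figures available. Applying them to a closed contralateral side over one year is an assumption.

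Low end: 211 × 0.20 × 0.002 = 0.08 children. High end: 211 × 0.60 × 0.003 = 0.38 children.

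Added PIRS risk is 0.20 × 0.002 = 0.04 points to 0.60 × 0.003 = 0.18 points. If all of it comes on top of the planned 1%, the PIRS rate becomes 1.04-1.18% and the difference 4.96-4.82 points instead of 5. Power at 422 falls from 80.0% to 79.2-76.0%, and the total needed for 80% becomes 432-466.

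These are upper figures for the strict gap. They count every closed contralateral side, whereas the gap proper concerns only sides where an actual hernia was closed. Section 4.4 also derives its 1% as the MCIH rate expected with CPPVs closed, so failures after CPPV closure are arguably already in it.

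**Sensitivity of the test.** Pearson chi-square with 13 open events, 211 per arm: p = 0.0038 with 2 PIRS events, 0.011 with 3, 0.026 with 4, 0.054 with 5. Three uncounted events on top of the planned 2 would be needed to cross 0.05. With an expected 0.38, the Poisson chance of three or more is 1 − e^(−0.38) × (1 + 0.38 + 0.072) ≈ 0.7%.

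**The case against.** The strongest reply is that most of the apparent gap closes on a natural reading. A CPPV is not yet a hernia. If it is closed and a hernia later appears on that side, that hernia is contralateral and later than the index hernia, hence an MCIH. Section 4.4 uses the term this way when it attributes the fall in the MCIH rate to 1% to closure of the CPPV. This stands. What remains is the contralateral hernia that was actually present, closed, and then recurred, and the protocol gives no frequency for it.

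A second reply is that the summary, objectives and section 4.4 show a broad intent. That also stands, but it does not settle the matter: the two sections that fix the endpoint and its test use the narrower wording.

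A third is that most of the data will exist anyway (number of operations per infant in section 8.3; side of the hernia, recurrence and contralateral hernia in section 12.1), and that a statistical analysis plan could hold the classification rule. This makes the correction easy. It does not remove a contradiction in the protocol's own primary endpoint.

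A reader might go further and infer that the wording biases the trial towards PIRS enough to decide it. If 20-50% of PIRS children had the side closed and 1-4% of closures failed, 211 × 0.20 × 0.01 = 0.4 to 211 × 0.50 × 0.04 = 4.2 children would be affected, as many as or more than the planned PIRS events at the upper end. The documents do not support this. It treats every closed CPPV as lying outside the endpoint, and its failure rates are several times the quoted 0.2-0.3%. Even with 60% closed, three expected failures require 3 / (211 × 0.60) = 2.4%, about eight times the higher of those rates.

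A reader might also see an open-arm counterpart in section 5.2, where "if a hernia or PPV is absent, the procedure is finished by closure of Scarpa fascia and skin": a later hernia on that side would follow no repair. Calling that non-recurrent is a strained reading, it would run in the opposite direction, and the same rewording covers it.

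**Conclusion.** The point holds as an inconsistency in the primary endpoint with a narrow, one-sided gap. The narrower wording does not clearly capture recurrence of a contralateral hernia closed at the index operation. By protocol that event arises only under PIRS, so any omission favours PIRS. The text does not show that all failed contralateral closures are excluded, because a hernia after CPPV closure reads most naturally as an MCIH.

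The expected effect is about 0.1-0.4 of 211 PIRS children, at most about 0.2 of the planned 5 percentage points. This rests on an assumed closed share of 20-60% and on carrying the quoted 0.2-0.3% recurrence rates over to the contralateral side. If closed sides failed at 1-2%, a stress assumption that the documents do not suggest, the figure would be 0.4-2.5 children. A changed trial result is not expected. The point still deserves correction: only about 2 PIRS events are planned, so one reclassified child would visibly move the relative risk, and classification would take place with the arm known.

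**What to change.** Use one definition in the summary, section 2, section 8.1.1 and section 10.1: a child with at least one operation for an inguinal hernia, on either side, within one year after the index operation, whatever was done on that side at the index operation.

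Add one sentence saying that this includes a hernia on a contralateral side where a hernia or a CPPV was closed at the index operation, and a hernia on a side where the index exploration found none. Record on the CRF, for each reoperation, the side and whether that side had been closed at the index operation, so that ipsilateral recurrence, MCIH and contralateral recurrence can be reported as components.

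The cost is a few lines of text and one CRF item. Treatment does not change, and the calculated 422 is unaffected at the stated rates. The downside is that the PIRS rate may become slightly less favourable.

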### **3. STUDY DESIGN**

A randomized controlled trial will be performed and 464 infants with a primary unilateral inguinal hernia will be randomized to either open repair or laparoscopic PIRS repair. All operations will be performed by experienced (laparoscopic) paediatric surgeons.

One and two years after surgery all children will be called by the researcher. Prior to this call, patients or their parents will be asked to send a photo of the subject groins.. The latter is done to score testicular atrophy, recurrence or contralateral hernia. This will also be scored during a video call two years post-surgery. It is not possible to blind children or their parents/caretakers or health care professionals for the study arm, since different scars will develop and instructions have to be given for the postoperative treatment of the wound(s).

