#### Assessment of study parameters/endpoints

The following applies to all infants admitted to the hospital for inguinal hernia repair included in this study.

Preoperative size of both testes, the number of operations per infant, length of hospital stay, total duration of operations (including anaesthesia) and perioperative complications of surgery (iatrogenic injury, apnoea) will be recorded in Case Report Forms by the (fellow) paediatric surgeon. One telephone call is performed by a member of the research team after four weeks in the control and intervention group to obtain information regarding recovery of the patient, wound healing and recurrence. Pre-operative and four weeks and one year post-operative, parents or patients older than 12 years of age (with the aid of their parents) will fill out an online questionnaire regarding health of the subject and cost-effectiveness. Invitations for the questionnaires will be sent by Castor EDC, in which the results also will be recorded (13). Furthermore one and two years after surgery telephone call is conducted to assess post-operative complications such as testicular atrophy and recurrence. Prior to the telephone consult, parents are asked to send a photo to the researcher with the help of a secured online application (SURFfilesender) and a coded number

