### **11.2 Recruitment and consent**

All children with an unilateral inguinal hernia visit the outpatient clinic of the (resident/fellow) paediatric surgeon with parents/caretakers. The surgeon explains the study, hands over the information letter and informed consent form to the parents/caretakers, and asks permission to hand over their contact details to the research team. All (fellow) surgeons that will be involved in the conduct of this clinical trial will receive training in order to provide information to the parents/caretakers, according to the SOP and GCP guidelines. Most children are operated within 3-4 weeks after the outpatient clinic visit. After a minimum of seven days, a medical researcher will call the parents/caretakers to ask if they will participate in this study and ask them to sign the two informed consent letters. If, however, the surgery is planned within a week after the outpatient clinic visit, the researcher will call the parents sooner than 7 days, after a minimum of 24 hours, so the parents have enough time to ask questions and think about possible participation. The parents are asked to send the consent letters by post. After receiving the signed informed consent letters, a member of the research team will sign the informed consent letter and randomize the patient using a web-based application. At the day of the surgery, a research team member will collect

the informed consent forms and also signs both forms. One informed consent form will be distributed to the parents/caretakers.

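### The primary event is defined in conflicting ways around the one-year mark, and the planned calls do not name the contralateral hernia or reoperation that drives it

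*Protocol*

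**What the plan says.** The protocol describes the primary outcome in four places.

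- **Section 8.1.1** counts infants with an "ipsilateral recurrent hernia or MCIH after operative repair requiring a reoperation within one year after primary surgery".
- **The summary** gives "Number of operations related to inguinal hernia within one year after inguinal hernia repair".
- **Section 2** gives "total of operations related to inguinal hernia within one year after inguinal hernia repair as primary outcome measure".
- **Section 10.1** builds the 2x2 table on "children with and without a ipsilateral recurrent or MCIH hernia in the year after surgery". It does not mention reoperation.

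On follow-up, section 8.3 plans a call at four weeks covering recovery, wound healing and recurrence. Section 3 then says: "One and two years after surgery all children will be called by the researcher". Families send a photo of the groins before each of these calls; its purpose is given as "The latter is done to score testicular atrophy, recurrence or contralateral hernia". Section 8.3 describes the same one- and two-year contacts differently: a "telephone call is conducted to assess post-operative complications such as testicular atrophy and recurrence". The surgeon records the number of operations per infant in the case report form.

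On waiting time, section 11.2 states: "Most children are operated within 3-4 weeks after the outpatient clinic visit". This refers to the primary repair.

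Section 4.4 sizes the trial on reoperation for metachronous contralateral inguinal hernia (MCIH), 6% open against 1% PIRS. It sets recurrence aside because the rates are similar (0.3% and 0.2%).

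**The concern.** Two things meet at twelve months: the end of the window for a countable reoperation and the only scheduled hernia check after week 4 within that window. A hernia first seen at that check cannot already have been repaired. Whether the child is an event then depends on which section is followed.

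In an unblinded trial this has a second side. If the reoperation must fall inside the year, booking an elective repair just before or just after the anniversary decides whether the child counts.

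Ascertainment is a related problem. Almost all expected events are contralateral, yet the listed call content does not name contralateral hernia or reoperation. A photo at one year cannot show that a contralateral hernia was repaired months earlier at another hospital, nor when. The case report form is completed by the paediatric surgeon, and the protocol states no route by which that surgeon learns of surgery elsewhere. The additional questionnaire after a reoperation (8.1.2) can be sent only once the reoperation is known.

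**Working it through.** **Step 1. The same child under each definition.** Section 8.1.1 is read here with the year attached to the reoperation, as the summary and section 2 imply.

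| Child | 8.1.1 | Summary and section 2 | 10.1 |
|---|---|---|---|
| MCIH diagnosed in month 6, repaired in month 7 | event | one operation | event |
| MCIH diagnosed in week 50, repaired 3-4 weeks later (week 53-54) | no event | none | event |
| MCIH first found at the one-year contact, repaired later | no event | none | event |
| Hernia in month 6, no reoperation | no event | none | event |
| Recurrence and MCIH, each reoperated within the year | one event | two operations | one event |

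If the year in 8.1.1 attaches to the hernia instead, rows 2 and 3 become events there, but row 4 still differs from 10.1. The wording of 8.1.1 does not settle which reading is meant.

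**Step 2. Reproduce the planned size.** The inputs from 4.4 and 8.2 are p1 = 0.06, p2 = 0.01, two-sided alpha 0.05, power 0.80 and 1:1 allocation. With p̄ = (p1 + p2)/2 = 0.035,

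n per arm = [1.960·√(2p̄(1−p̄)) + 0.842·√(p1(1−p1) + p2(1−p2))]² / (p1−p2)²

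= [1.960 × 0.2599 + 0.842 × 0.2575]² / 0.05² = 210.9, so 211 per arm and 422 in total. This is the stated figure. Power at 211 per arm is 80.0%. Expected events are 211 × (0.06 + 0.01) = 14.8, about 15.

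**Step 3. Illustrate the window loss.** Two assumptions are needed that the protocol does not supply: hernias arise evenly over the year, and reoperation follows detection by the 3-4 weeks given for the primary repair. The share falling outside the window is lag/52, and both rates are multiplied by 1 − lag/52. Power is Φ{[√211·(p1−p2) − 1.960·√(2p̄(1−p̄))] / √(p1(1−p1) + p2(1−p2))}.

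| Lag | Share outside | Rates | Events outside | Power, 211 per arm |
|---|---|---|---|---|
| 0 | 0 | 6.00% v 1.00% | 0 | 80.0% |
| 3 weeks | 3/52 = 5.8% | 5.65% v 0.94% | 0.85 | 77.5% |
| 4 weeks | 4/52 = 7.7% | 5.54% v 0.92% | 1.14 | 76.6% |

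The loss is proportional in both arms, so the ratio of the two rates stays at 6. The absolute difference falls from 5.0 to 4.7 or 4.6 percentage points.

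**Step 4. Contralateral hernia across the sections.** It is named in section 3 (photo, and the two-year video call), in 8.1.2 (MCIH rate within one year) and in 12.1 (data to be collected). It is not named in the 8.3 description of any call.

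**The case against.** A reader might infer that late hernias drop out of the primary endpoint altogether. The documents do not support this: under 10.1, which governs the primary test, a hernia found by the one-year contact counts. What stands is the contradiction between 10.1 and the other three places.

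A reader might also infer that the one-year contact adds nothing to the endpoint. That is too strong. It can reveal a reoperation done earlier in the year, and contact at the end of the window is normal for a one-year endpoint. Hernias that present and are repaired during the year do not depend on the call at all.

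Nor is contralateral hernia missing from follow-up. Sections 3, 8.1.2 and 12.1 plan to record it, and the list for the one- and two-year calls in 8.3 is given as examples. What stands is a mismatch between sections 3 and 8.3, and the lack of any stated question about surgery elsewhere.

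The power figures are open to challenge. The 6% planning rate is already described as a reoperation rate, so taking a waiting time off it may count the delay twice. It is also the low end of the 6-8% cited in 4.4: with the full four-week loss in both arms, power is still 85.7% starting from 7% and 91.7% from 8%. These objections stand, and the figures serve only as illustration.

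Finally, a dated operation is a harder event in an unblinded trial than a diagnosis. This is fair, and the fix has to allow for it. A statistical analysis plan, not shown here, might choose one definition. The protocol would still contradict itself, and an analysis plan written later cannot recover call answers that were never collected.

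**Conclusion.** The point holds as an inconsistency in the primary event with an avoidable gap in ascertainment. The inconsistency needs no assumption: it follows from comparing 8.1.1, the summary and section 2 with 10.1. The children affected are those whose hernia is first found at or shortly before one year, and those with a hernia but no reoperation.

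The size is modest. Under even onset and a 3-4 week wait, about 1 of 15 expected events changes status and power moves from 80.0% to about 77%, with the relative risk unchanged. Larger losses, such as 10-20% of events, might be suspected, but the protocol gives no basis for them. Events missed because surgery took place elsewhere cannot be quantified from the document.

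It is worth correcting because the change is cheap and the expected number of events is small.

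**What to change.** **One definition.** Use the same event in 8.1.1, section 2, the summary and 10.1, counted per child. For example: an ipsilateral recurrence or MCIH diagnosed up to and including the one-year contact, for which a reoperation is performed, confirmed from the operation record or at the two-year call already planned. Requiring a performed rather than a scheduled reoperation keeps the event verifiable. Add reoperation performed within one year of primary surgery as a sensitivity analysis.

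**Direct questions.** In 8.3, have the four-week, one-year and two-year calls ask explicitly about a contralateral hernia and about any groin operation at any hospital, with its date. Bring the description of these contacts into line with section 3.

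**Cost.** Wording and call scripts; no new contact and no change in treatment. There are two downsides. Late reoperations must be awaited for a short time before the primary outcome is complete. For children withdrawn from treatment, for whom 8.6 seeks permission only for a one-year call, confirmation would rest on the operation record. A diagnosis date in an unblinded trial is also open to some detection bias; requiring a performed reoperation and running the sensitivity analysis limit it.
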